#### Trial design

3.2.1

A single‐blinded, multicentre, randomized, controlled, parallel‐group pre‐test, and repeated post‐test design will be conducted to investigate the effect of the ISP for Chinese primiparous women in the initial postpartum period. The study follows the SPIRIT 2013 Statement and the guidelines for the Standard Protocol of Clinical Trials (Chan et al., 2013). The Consolidated Standards of Reporting Trials (CONSORT) (Schulz, 2011) flowchart is presented in Figure 2.

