#### Randomization and blinding

3.2.4

The Research Randomizer will be used to randomly assign participants into the experimental group and the control group with a distribution ratio of 1:1. The allocation sequence will be put into the opaque and sealed envelopes. Blinding will not be possible for the researchers during all the research process; however, the group allocation will be masked during the recruitment until the baseline measures are completed. In terms of trial participants, outcome assessors, and data analysts, they will be blinded to the participants’ group allocation.

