**Figure 3 jan14517-fig-0003:**
[figure not shown]
ISP program and its five modules. Note: TA, Technical assistants; ISP, Internet‐based support program [Colour figure can be viewed at wileyonlinelibrary.com]

The researchers will teach women in the intervention group how to log in and use each module of ISP by mobile phone or computer. The original username and password of women will be setup by the researchers; and can be changed by women later. The frequency and duration of the logins will be monitored to evaluate the women's adherence. Technical assistance will be available on the weekdays by telephone or email.

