#### Data collection procedure

3.2.7

The baseline assessment will be conducted by the researchers and every participant will be asked to complete the SICS, EPDS, PSSS, and social‐demographic and clinical data in the obstetric wards. Post‐test 1 will be carried out immediately after the intervention and Post‐test 2 will be conducted on 3 months after the intervention. At the two time points of Post‐tests 1 and 2, the questionnaires comprised of SICS, EPDS, PSSS, and healthcare satisfaction will be sent to participants by wechat or email; and the completed questionnaires will be returned to the researchers by wechat or email. To improve the response rate, a kindly telephone or wechat reminder will be given to participants before and after one week of the two time points, respectively.

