### Validity and reliability

3.4

This study adopts the rigorous research design, such as the sound theoretical framework, a RCT design with a good representative and predetermined sample, the use of instruments with a high validity and reliability, and statistically scientific analysis, which can be seen to reduce bias effectively and enhance the generalizability of research results beyond the target population. Moreover, outcome assessors and data analysts of the research will be blinded after assignment to interventions to reduce the biases in evaluation of the effects of the intervention.

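### Participants and outcome assessors are declared blinded, but women know their arm and rate every effectiveness outcome themselves; only the data analysts can be blind

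*Protocol article*

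**What the plan says.** Section 3.2.4 (Randomization and blinding) makes three statements:

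- On researchers: "Blinding will not be possible for the researchers during all the research process".
- On the period before allocation: "the group allocation will be masked during the recruitment until the baseline measures are completed".
- On everyone else: "In terms of trial participants, outcome assessors, and data analysts, they will be blinded to the" group allocation.

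The abstract and section 3.2.1 call the trial single-blinded. Section 3.4 (Validity and reliability) relies on part of this as a safeguard: "outcome assessors and data analysts of the research will be blinded after assignment to interventions to reduce the biases". Section 4.1 (Limitations) gives the researchers' lack of blinding as a possible source of bias and does not mention the participants.

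On delivery, section 3.2.5 says: "The researchers will teach women in the intervention group how to log in and use each module of ISP". Table 1 adds weekly telephone reminders to log in, for the intervention arm only, and gives the control arm routine care. On collection of the post-test questionnaires, section 3.2.7 says: "the completed questionnaires will be returned to the researchers by wechat or email".

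**The concern.** The article claims blinding for two parties who cannot be blind under its own description of the intervention and the measurements. This is a positive statement that the rest of the text contradicts, so condensation from a fuller protocol does not explain it.

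Mood, confidence in infant care, perceived support and satisfaction are subjective. A woman who knows she received the program may answer more favourably. A woman who was told of it and did not get it may answer less favourably out of disappointment. Either would move the group difference in the direction the trial hopes to show. A reader or risk-of-bias assessor who takes sections 3.2.4 and 3.4 at face value would credit the trial with a protection it does not have, on all three primary outcomes and on the secondary one.

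**Working it through.** The point is settled by comparing sections; the arithmetic at the end only gives scale.

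**Can participants be blind after allocation?**

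| Section | What it establishes |
|---|---|
| 3.2.3 Recruitment | Nurses describe the ISP to eligible women, and posters and leaflets on the wards do the same, so women know the program exists before allocation. |
| 3.2.5 Intervention | Intervention women have an account set up for them and are taught each module by the researchers. |
| Table 1 | Intervention women are telephoned weekly about logging in, over at least 12 weeks. Controls have routine care only; no sham site or attention control is described. |

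An intervention woman knows she has the program. A control woman who was told of it and received no login knows she does not. Participants are therefore unblinded.

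**Can outcome assessors be blind?**

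| Outcome | Who supplies the rating |
|---|---|
| SICS (primary) | The woman: items scored 0–100, on a questionnaire sent to her (3.2.6, 3.2.7) |
| EPDS (primary) | The woman: described as self-report, 0–30 (3.2.6) |
| PSSS (primary) | The woman: described as self-report, 0–60 (3.2.6) |
| Satisfaction (secondary) | The woman: three-item questionnaire sent to her (3.2.6, 3.2.7) |

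For all four, the assessor is the unblinded woman. Login tracking is objective, but it measures use of the program and is not an effectiveness outcome. Two further details point the same way. Completed forms go back to the researchers, the one group that section 3.2.4 says cannot be blinded. The ISP's reminder module also includes a prompt to fill in questionnaires, which controls do not see, although both arms get the telephone or WeChat reminder in section 3.2.7.

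**What remains of the claim?** Analyst blinding is feasible. Masking until baseline is complete protects the baseline scores. Neither protects answers given at post-test 1 or post-test 2.

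**Scale on the EPDS.**

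- Inputs: planned effect 0.35 SD (3.2.2); EPDS SDs of 3.33 and 3.97 in the earlier Chinese trial described in section 1.
- Pooled SD = √[(3.33² + 3.97²)/2] = √13.42 = 3.66.
- Planned effect in points = 0.35 × 3.66 = 1.28.
- Assumed reporting shift of 0.6 points: 0.6/1.28 = 47% of the planned effect.

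**Chance of a significant result with no true effect.** Take n = 90 analysed per group, the plan's figure before attrition (90/0.70 = 128.6, rounded up to the stated 129). Let b be a reporting shift in SD units. With a two-sided test at 0.05 and m = b/√(2/90) = b/0.149, the probability is 1 − Φ(1.96 − m) + Φ(−1.96 − m).

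| b (assumed) | EPDS points | Chance of significance |
|---|---|---|
| 0 | 0 | 5% |
| 0.1 | 0.37 | 10% |
| 0.2 | 0.73 | 27% |
| 0.3 | 1.10 | 52% |
| 0.35 | 1.28 | 65% |

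The calculation uses a simple two-group comparison of EPDS means, not the planned multivariate model. The documents give no value for b.

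**The case against.** The strongest reply concerns scope and severity.

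- **Part of the protection is real.** Section 3.4 credits assessors and analysts, not participants, and analysts can be blind. Allocation is also hidden until baseline is complete. This stands: the criticism covers participants and assessors only, and the section 3.4 correction concerns assessors only.
- **The participant sentence might mean masking up to baseline.** Section 3.2.4 covers that period in its preceding sentence and then makes a separate, unrestricted claim for participants. The text does not support the narrower reading.
- **Returning forms to researchers does not alter fixed answers.** This is fair. No section has researchers scoring or changing post-test data. The return route is a secondary weakness; the main bias arises in the woman's own answers.
- **The single-blinded label is a matter of terminology.** Also fair. It sits badly with three parties listed as blinded, but it adds no bias of its own.
- **The size of the bias is assumed.** Correct. The 0.6-point shift and the table of b values show scale and are not evidence that bias of that size will occur.
- **The fix leaves the bias in place, so it is only disclosure.** It does not remove the bias, because women cannot be blinded to this program. It does change what the trial may claim from every one of its effectiveness outcomes.

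**Conclusion.** The concern holds. The claims that participants and outcome assessors are blinded are wrong as written. Sections 3.2.3 and 3.2.5, with Table 1, show that women will know their arm, and sections 3.2.6 and 3.2.7 show that the same women supply all four effectiveness outcomes. Analyst blinding and pre-baseline masking can stand, but they do not protect post-test self-reports.

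This conclusion rests on no numerical assumption. The scale does: if the EPDS SD is near 3.66, the target effect is about 1.3 points, and an assumed shift of 0.1 to 0.3 SD would raise the chance of a falsely significant EPDS difference from 5% to between 10% and 52% at 90 per group. An open-label comparison with routine care is a legitimate design. The fault lies in claiming blinding it cannot have and leaving the consequence out of the limitations. This must be corrected.

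**What to change.** 1. **Abstract and section 3.2.1:** replace the single-blinded label with a description of the trial as open-label for participants and researchers, with self-reported outcomes and blinded data analysis.
2. **Section 3.2.4:** remove participants and outcome assessors from the list of blinded parties. Keep the analysts and the masking until baseline.
3. **Section 3.4:** remove the outcome-assessor claim and keep the analyst claim.
4. **Section 4.1:** add that participants know their allocation and report all effectiveness outcomes themselves, with response bias and control-arm disappointment as possible consequences.
5. **Conclusions and later reports:** describe effects as self-reported outcomes under open-label conditions.
6. **Section 3.2.7, as a supporting measure:** have both arms complete one identical online form under the study code that goes straight to the database, so that unblinded researchers do not receive or handle completed questionnaires. This can apply to any post-tests still to be collected. It limits handling concerns but does not remove bias in the women's answers.

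The cost is protocol wording plus one standard online form. The trial gives up the blinding claim for participants and assessors. Arms, sample size, instruments and planned analysis are unaffected.

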#### Intervention

3.2.5

The women in the control group will receive routine care. Routine care consists of supports from the obstetricians and obstetric nurses during the 3–5 days hospitalization; and home visits from the community doctors on the 3rd, 7th, 14th, and 28th days postpartum (Zheng, Morrell, & Watts, 2015). The women in the study group will have access to the ISP and receive routine care in the postpartum period. The details of intervention are described in Table 1.

**Table 1 jan14517-tbl-0001:** The details of intervention

	Intervention Group	Control Group
Service	ISP + routine care	Routine care
Provider	Researchers	Obstetricians, obstetric nurses, community doctors
Place	Web environment	Hospital, home
Form	Internet	Face‐to‐face
Contents	Learning forum Communication forum Ask‐the‐expert forum Baby home forum Reminder forum	Routine postpartum home visiting
Duration and frequency	From childbirth to 3‐month postpartum The total intervention time not less than 12 weeks Reminder telephones every week, reminding them to log in the ISP at least twice a week, and no less than total 1 hr per week	From childbirth to 1 month postpartum At least two home visits
Assessment	Baseline (pre‐intervention) Post‐test 1 (immediately after intervention) Post‐test 2 (3 months after intervention)	Baseline (pre‐intervention) Post‐test 1 (immediately after intervention) Post‐test 2 (3 months after intervention)

Abbreviations: ISP, Internet‐based Support Program.

ISP (Figure 3) has a fixed structure and lasts approximately 3 months. Five modules are designed to meet learning needs, communication needs, emotional needs, and presentation needs for primiparous women. Module 1 is learning forum of parenting knowledge and skills showed by multimedia resources, such as text, picture, and video. The contents include: (1) Prevention, judgment, and intervention of common diseases for infants, such as eczema, pathological jaundice, diarrhoea, constipation, cough, allergy, fever, trachea foreign body, pneumonia, and thrush; (2) Daily care: including dressing, changing diapers, bathing, dietary feeding, umbilical cord care, sleep problems, urinary and faecal problems, prevention of accidental injury, and other safety issues, etc; (3) Growth and development: including normal and abnormal performance of newborn babies, e.g., motor ability, language ability, socialized emotion, and socialized development; baby touch and parent–child interaction; and (4) Postpartum care: including coping with postpartum physical and mental changes, postpartum exercise for women, etc. Module 2 is communication forum where new mothers can tell their parenting stories, exchange parenting experiences, seek resonance, and belonging. Women are also invited to discuss some topics in this forum such as the transition to motherhood, Chinese traditional practice of “Doing the month”, obstacles to communication, potential interpersonal conflict after childbirth, and skills for resolving interpersonal conflicts. Ask‐the‐experts forum is module 3 and health professionals can interact with primiparous women, answer their parenting question posted by individuals within 24 hr. Some self‐test tools for baby also are included to help new mother to get some useful information, such as Bayley Scales of Infant and Toddler Development (BSID), growth and development curve for Chinese children, baby immunization query, etc. Baby home forum is module 4 where mothers can record and share their babies’ growth and their feelings. Some early education multimedia resources likewise are in this forum, such as children's songs, animation, story, and ancient poetry. Module 5 is reminder forum, including ISP learning reminder, postpartum physical examination reminder, and questionnaire filling reminder.

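### A questionnaire reminder is built into the internet program, so only intervention women get this extra outcome prompt, with a risk of differential response at post-test 1

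*Protocol article*

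**What the plan says.** Section 3.2.5 (Intervention) lists the five modules of the internet-based support program (ISP). On the last it says: "Module 5 is reminder forum, including ISP learning reminder, postpartum physical examination reminder, and questionnaire filling reminder". Access is by arm: "The women in the study group will have access to the ISP and receive routine care in the postpartum period". Control women receive routine care only.

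Table 1, in the intervention column only, adds "Reminder telephones every week, reminding them to log in the ISP at least twice a week, and no less than total 1 hr per week". In the same cell the duration is a minimum: "The total intervention time not less than 12 weeks".

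Section 3.2.7 (Data collection procedure) sets the follow-up procedure for both post-tests without distinguishing the arms. The questionnaires "will be sent to participants by wechat or email; and the completed questionnaires will be returned to the researchers by wechat or email", and "a kindly telephone or wechat reminder will be given to participants before and after one week of the two time points, respectively".

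Section 3.2.2 allows for 30% attrition as one overall figure. Section 3.2.8 names intention-to-treat analysis as the way to manage missing data.

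**The concern.** The procedure for obtaining outcomes should be the same in both arms, so that who answers does not depend on allocation. Here one outcome prompt is delivered through the treatment under test. Control women cannot receive it, and intervention women also have a weekly call from the trial up to about the time of post-test 1.

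Three features of this trial give that some weight. All three primary outcomes (SICS, EPDS, PSSS) are self-reported and returned remotely. The plan itself expects sizeable loss. And analysing women as randomized does not by itself remove bias when outcomes are missing at different rates in the two arms for reasons linked to the outcome. If extra prompting changes who responds, the EPDS comparison among responders shifts even when the program has no effect.

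A lesser matter is the label. Table 1 gives the form of the intervention as internet, and the Impact statement and section 5 speak of the effectiveness of an internet platform, whereas the package tested also includes weekly telephone calls.

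**Working it through.** **Step 1. Which prompts reach which arm**

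| Prompt | Source | Intervention | Control |
|---|---|---|---|
| Telephone or WeChat reminder around post-tests 1 and 2 | 3.2.7 | yes | yes |
| Questionnaire reminder in Module 5 | 3.2.5 | yes | no |
| Weekly log-in call | Table 1 | yes | no |

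The first row is a common base. The second is an outcome prompt in one arm only. The third is not an outcome prompt, since its stated purpose is logging in, but it is regular contact with the trial in one arm only. At 12 weeks, the stated minimum, and 129 women per arm, it amounts to at least 12 × 129 = 1,548 calls against none.

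**Step 2. Timing**

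The program lasts about 3 months. Post-test 1 follows at once, and post-test 2 comes 3 months later. Module 5 is therefore live in the run-up to post-test 1. The article does not say whether its prompts, or the calls, continue after the program ends. The imbalance is clear only for post-test 1.

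**Step 3. The plan's attrition figure**

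90 / (1 − 0.30) = 128.6, rounded up to 129 per arm and 258 in total, as stated. The 30% is not split by arm, so any gap between the arms below is an assumption.

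**Step 4. What a gap in response would do**

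Assumptions:
- EPDS is standard normal in both arms, so there is no true effect.
- The dropout probability is p(x) = 1 / (1 + exp(−(a + b·x))), with b = 0.5 or 0.7 per SD of EPDS.
- In each arm, a is set so that the average of p(x) equals the assumed loss.
- The mean among completers is E[x(1 − p(x))] / (1 − loss), found by numerical integration.

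| Loss | Completer mean, b = 0.5 | Completer mean, b = 0.7 |
|---|---|---|
| 15% | −0.073 | −0.099 |
| 25% | −0.120 | −0.161 |
| 30% | −0.143 | −0.192 |

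Intervention minus control, in SD:

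| Loss, intervention v control | b = 0.5 | b = 0.7 | Share of 0.35 |
|---|---|---|---|
| 30% v 30% | 0 | 0 | 0 |
| 25% v 30% | 0.023 | 0.031 | 7% to 9% |
| 15% v 30% | 0.070 | 0.093 | 20% to 27% |

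For scale in EPDS points, the Introduction quotes SDs of 3.33 and 3.97 from an earlier Chinese trial. Pooled, that is √((3.33² + 3.97²)/2) = 3.66. The four non-zero differences are then about 0.08, 0.11, 0.26 and 0.34 points.

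**Step 5. Direction**

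With b positive, more depressed women drop out and the control arm loses more of them. Control completers then look less depressed than they should, and the difference runs against the ISP. With b negative, the sign reverses and the ISP is flattered. With equal loss and the same b in both arms, the difference is zero.

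**The case against.** The strongest reply is that section 3.2.7 already gives every participant the same questionnaires, the same return route and a reminder around both post-tests. One more prompt inside an app may add little, and nothing suggests that it would halve attrition. With a 5-point gap the distortion is under a tenth of the planned effect. The calculation is also a raw completer comparison, whereas the planned model includes baseline as a time point and sociodemographic covariates. A CONSORT flowchart is planned, and it would normally show follow-up by arm.

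Most of this stands as a limit on size. It does not answer the point itself: the common reminders are a base on which one arm receives more, and removing the difference costs almost nothing.

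Stronger readings that a reader might infer are not supported:
- *That the trial creates unequal follow-up.* The documents show unequal prompting. They neither state nor predict different attrition by arm.
- *That any bias would produce a false positive.* If more depressed women drop out, the bias hides an EPDS benefit.
- *That the calls run for at most 12 weeks, or that they deliver support.* Table 1 gives 12 weeks as a minimum, and the only stated purpose is to prompt log-ins. Supportive content would be inference.
- *That comparing the package with routine care is invalid.* It is a legitimate design, and Table 1 discloses the calls. The attribution point is one of wording.

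**Conclusion.** The point holds as one of unequal prompting. An outcome reminder sits inside the intervention, control women cannot receive it, and weekly calls add contact in the same arm. This creates a risk of differential response on remotely returned self-report outcomes. The risk is clear at post-test 1 and undetermined at post-test 2.

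The size is unknown, because no response rates by arm are given. Under the assumptions in the working, the completer difference is about 0.02 to 0.03 SD for a 5-point gap in loss and 0.07 to 0.09 SD for a 15-point gap. Its sign depends on who fails to respond. The larger figure would matter against a planned 0.35; the smaller would hardly be noticed. The case for change rests on how easily the imbalance can be avoided, not on a demonstrated bias. The labelling of the intervention is a minor wording remark.

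**What to change.** 1. Take the questionnaire reminder out of Module 5, or send control women the same message on the same dates by WeChat, so that outcome reminders are identical in both arms. The log-in and physical examination reminders can stay where they are.
2. If the Module 5 message is kept and matched, say whether it continues to post-test 2.
3. Report response by arm at each post-test.
4. Minor: in the aim and conclusions, describe the tested intervention as the ISP plus weekly telephone log-in reminders.

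The cost is a website setting or a few automatic messages, plus a few words of text. The downside is a slightly narrower claim: the result would speak for the program with calls, not for the internet platform alone.
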